### Interventions

#### Immediately delivery

In the intervention group labour will be induced within 24 hours after randomisation. Induction of labour consists of amniotomy and augmentation of labour by administration of oxytocine. In case of an unfavourable cervix induction of labour will be preceded according to the local protocol. Prostaglandins will not be administered to women with a history of caesarean section. Cervical dilatation in these women will be achieved by a cervical Foley catheter followed by amniotomy and augmentation of labour with oxytocine. In case the patient gives no consent for vaginal delivery (for example breech presentation or history of two caesarean sections) the patient will be delivered by caesarean section within 24 hours after randomisation. After delivery, all patients in the intervention group will be monitored clinically.

#### Expectant monitoring until 37 weeks

In the expectant monitoring group, patients will be monitored until the onset of spontaneous delivery. If onset of labour has not occurred at 37^+0 ^weeks gestation, labour will be induced. Monitoring will consist of assessment of fetal movements as reported by the mother, as well as electronic fetal heart rate monitoring at least twice a week. Maternal evaluation consists primarily of frequent evaluation of blood pressure measurement and screening of urine for protein using a dipstick or protein/creatinin ratio twice a week (24 hour urine collection for protein in case of positive screening). Blood tests (platelet count, liver enzymes and renal function) will be performed in case of abnormal maternal blood pressure and/or proteinuria. In the expectant monitoring group, intervention is recommended in case the fetal or maternal condition does not justify expectant monitoring anymore. These criteria are similar to the exclusion criteria of the trial. All patients in the expectant monitoring group will be monitored clinically until after delivery.

#### Follow-up of women and infants

All details of delivery, maternal and neonatal assessments and admission during pregnancy are recorded in the CRF that is accessible through the website. Mortality and morbidity will be specified for the mother and the child until date of discharge from hospital and six weeks postpartum.

We plan long term follow-up at the age of 2 years with the Ages & Stages Questionnaires (ASQ) and the Child Behavioral Checklist (CBCL). By means of e-mails generated by our web-based registration system, our research nurses will be notified when a child approaches the corrected age of two years. After this alert, the research nurse will approach the parents of the child by phone and announce the sending of the questionnaire. In case the parents do not return the questionnaire, a reminder will be sent. We use the validated Dutch translation of the ASQ, covering the age-range 4-60 months and the validated Dutch translation of the CBCL 11/2 - 5 years [12]. The ASQ is developed as a developmental screener and has been validated to pick up children at risk of a developmental disability. The CBCL (Child Behavioral Checklist) evaluates maladaptive behavioral and emotional problems in children reported by parents. It assesses internalizing (i.e., anxious, depressive, and overcontrolled) and externalizing (i.e., aggressive, hyperactive, noncompliant, and undercontrolled) behaviors. We will compare the total mean scores and T-scores between study arms and in addition we will compare the number of children scoring at 2 standard deviations below the mean of the Dutch reference group. A plan for long term follow-up of the mothers on their cardiovascular risk in the future is in preparation [13].

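### The two-year cut-off of 2 SD below the Dutch reference mean is not limited to the ASQ; applied to the CBCL, which measures problems, it counts the wrong tail

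*Protocol article*

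**What the plan says.** The section 'Follow-up of women and infants' of the protocol article plans a two-year assessment with two parent questionnaires, the ASQ and the CBCL. It describes what each is for:

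- ASQ: "The ASQ is developed as a developmental screener and has been validated to pick up children at risk of a developmental disability".
- CBCL: "The CBCL (Child Behavioral Checklist) evaluates maladaptive behavioral and emotional problems in children reported by parents". It adds: "It assesses internalizing (i.e., anxious, depressive, and overcontrolled) and externalizing (i.e., aggressive, hyperactive, noncompliant, and undercontrolled) behaviors".

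A single sentence of analysis follows directly on the CBCL description. Its first half reads "We will compare the total mean scores and T-scores between study arms". Its second half sets the threshold: "we will compare the number of children scoring at 2 standard deviations below the mean of the Dutch reference group". Neither half says which instrument it refers to. No other cut-off for either questionnaire, and no upper cut-off, appears in the document.

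**The concern.** The rule fixes a direction, below the reference mean, and leaves open which instrument it covers. For a developmental screener on which low scores are adverse, that direction is sensible. For an instrument that records problems it is not: a child far below the reference mean has unusually few problems, and the children of interest are far above it.

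Direction matters here because of what the trial sets out to weigh. Under 'Aims', the stated hypothesis is a maternal gain from induction at the price of more neonatal morbidity. The two-year questionnaires are the only planned look at later development and behaviour. A count taken in the wrong tail of the CBCL would not show an excess of children with behavioural problems, and under some score distributions it would move the opposite way.

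**Working it through.** **Inputs from the document.** A threshold of 2 SD; direction below the mean; reference group Dutch; CBCL described as evaluating problems. The document gives no expected rate, power or sample size for the two-year comparison, so there is no planned figure to reproduce.

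**Inputs assumed.** A higher CBCL score means more problems (inferred from the description, not stated). Scores are normal with the reference mean and SD in one arm. The other arm is shifted by d SD towards more problems, with d from 0.1 to 0.5. Neither the normal shape nor the shift comes from the protocol.

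**Step 1: the two tails under a normal score.** With Φ the standard normal distribution function:

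- tail counted by the rule (below −2 SD): Φ(−2 − d)
- tail holding the impaired children (above +2 SD): 1 − Φ(2 − d)

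| Shift d (SD) | Below −2 SD, counted | Above +2 SD, impaired |
|---|---|---|
| 0 | 2.28% | 2.28% |
| 0.1 | 1.79% | 2.87% |
| 0.2 | 1.39% | 3.59% |
| 0.3 | 1.07% | 4.46% |
| 0.5 | 0.62% | 6.68% |

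As problems increase, the counted share falls and the impaired share rises, for every shift tried.

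**Step 2: what this means in children.** Take 340 per arm (half of the planned 680), one child per woman and complete response. At d = 0.3 the rule would count 340 × 0.0228 = 7.8 children in the unshifted arm and 340 × 0.0107 = 3.6 in the shifted arm. Counting the upper tail gives 7.8 and 340 × 0.0446 = 15.2. Non-response would lower these numbers and multiple pregnancies would raise them; the direction stays the same.

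**Step 3: a skewed score.** A count of problems cannot be negative and may be right-skewed. Take a gamma distribution with mean 1 and coefficient of variation CV, so that the SD equals CV, the shape is 1/CV² and the lower cut-off is 1 − 2 × CV.

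| CV (assumed) | Lower cut-off | Share below it | Share above mean + 2 SD |
|---|---|---|---|
| 0.3 | 0.4 | 0.5% | 3.6% |
| 0.4 | 0.2 | 0.1% | 4.0% |
| 0.5 | 0 | 0% | 4.2% |
| 0.6 | −0.2 | 0% | 4.5% |
| 0.8 | −0.6 | 0% | 4.8% |

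From CV 0.5 on, the lower cut-off is at or below zero and no child can score under it. In that case the count is empty and gives no information in either direction.

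**The case against.** The strongest reply is that the sentence summarises two instruments at once. It lists two types of score without assigning them, and the cut-off may likewise be meant for one instrument only, the developmental screener. On that reading nothing points the wrong way. The CBCL simply has no threshold in the article, and a condensed article may leave that to the full protocol. This reading is possible and cannot be excluded. It does not remove the need for a correction, because the rule as printed follows the CBCL description, is not restricted to the ASQ, and states a direction that does not fit an instrument of problems. That is a stated rule that does not fit, not a missing detail.

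Three further points stand:

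- The same sentence also compares mean scores and T-scores, and these are unaffected. An arm with more behavioural problems could still be seen there.
- A near-empty CBCL count, as in the skewed case, would probably be noticed before it misled anyone.
- The reach is small. The questionnaires are not among the measures listed under 'Outcome measures', are not covered under 'Data analysis' and do not enter 'Sample size'. Under 'Aims', the long-term follow-up is described as still to be worked out.

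A reader might infer that the plan definitely applies the lower cut-off to both questionnaires, and that its behavioural comparison is therefore reversed and would make early delivery look safer. The document does not support that. It does not assign the rule to the CBCL by name, a reversed count arises only for some score shapes, and the mean comparisons beside it keep the right direction.

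**Conclusion.** The point holds in a limited form. The article gives one two-year threshold in one direction and does not confine it to the instrument for which that direction makes sense. If it is applied to the CBCL, the count is misdirected under roughly normal scores: 1.79% down to 0.62% counted, against 2.87% up to 6.68% impaired, for shifts of 0.1 to 0.5 SD. With a strongly right-skewed score it is nearly or completely empty.

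These sizes rest on assumed distributions and shifts. The direction rests only on the article's own description of the CBCL as evaluating problems. The defect is confined to the two-year dichotomous comparison and does not touch the trial's main conclusions. It is worth correcting because a threshold fixed in advance should not depend on the analyst silently choosing the other tail.

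**What to change.** Replace the threshold clause with one that names each instrument and its adverse direction: for the ASQ, the number of children scoring 2 SD or more below the Dutch reference mean; for the CBCL problem score, the number scoring 2 SD or more above it. The ASQ direction takes low scores as adverse. The article's rule implies this but does not state it, so the scoring direction of each questionnaire should be confirmed in the same place. The cut-offs are best kept in SD units, since the article does not give the T-score scale.

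The cost is one sentence in the protocol or analysis plan. Data collection, the questionnaires, the comparison of mean scores and the sample size do not change.

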### Outcome measures

#### Primary outcome measure

The primary outcome measure will be a composite endpoint of maternal mortality, maternal complications (eclampsia, HELLP syndrome, pulmonary oedema, thromoembolic disease) and progression to severe pre-eclampsia. Eclampsia is defined as severe gestational hypertension or pre-eclampsia resulting in maternal seizures [14]. HELLP syndrome is defined as a complication of severe pre-eclampsia involving Hemolysis, Elevated Liver functions, and Low Platelets [14,15]. Thromboembolic disease is defined as deep-vein thrombosis, pulmonary embolism or both. Patients will be examined for deep-vein thrombosis by duplex Doppler if thrombosis is suspected from clinical examination. A diagnosis of pulmonary embolism will be confirmed by pulmonary angiography, computed tomography, magnetic resonance imaging or a ventilation-perfusion lung scan [16-18].

Progression to severe pre-eclampsia is defined as diastolic blood pressure equal/greater than 110 mmHg despite medication, systolic blood pressure equal/greater than 170 mmHg despite medication and/or proteinuria equal to/greater than 5 g/L.

The neonatal primary outcome will be respiratory distress syndrome (RDS). Diagnosis of RDS requires signs of respiratory distress, consistent radiologic features, and oxygen therapy with a fraction of inspired oxygen (FIO2) of 0.40 or greater for at least 24 hours or until death [19].

Secondary outcome measures

Secondary maternal outcomes will be caesarean section rate, instrumental vaginal delivery rate, maternal quality of life and costs. Secondary neonatal outcomes will be transient tachypnoe of the newborn, hypoglycaemia, newborn sepsis, confirmed seizures, necrotizing enterocolitis, hypoxic-ischemic encephalopathy, cardiopulmonary resuscitation or ventilator support within 24 hours after birth, umbilical-cord-blood arterial pH below 7.0, a 5-minute Apgar score of 3 or below, admission to the neonatal intensive care unit (NICU) or neonatal death [19]. Transient tachypnoe of the newborn is defined by the presence of tachypnoe within hours after birth and typical radiologic findings. The diagnosis of necrotizing enterocolitis requires confirmation by radiologic findings, surgery, or autopsy. The diagnosis of hypoglycaemia requires a serum or plasma glucose level of less than 35 mg per decilitre (1.9 mmol per litre) and treatment with intravenous glucose. Newborn sepsis includes both suspected infections (with clinical findings suggesting infection) and proved infections (as confirmed in a subgroup of neonates with positive cultures of blood, cerebrospinal fluid, or urine obtained by catheterization or suprapubic aspiration; cardiovascular collapse; or an unequivocal radiograph confirming infection in a neonate with clinical sepsis).

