**Methods/Design:**

Pregnant women with severe gestational hypertension, mild pre-eclampsia or deteriorating chronic hypertension at a gestational age between 34^+0 ^and 36^+6 ^weeks will be asked to participate in a multi-centre randomised controlled trial. Women will be randomised to either induction of labour or expectant monitoring. In the expectant monitoring arm, women will be induced only when the maternal or fetal condition detoriates or at 37^+0 ^weeks of gestation. The primary outcome measure is a composite endpoint of maternal mortality, severe maternal complications (eclampsia, HELLP syndrome, pulmonary oedema and thromboembolic disease) and progression to severe pre-eclampsia. Secondary outcomes measures are respiratory distress syndrome (RDS), neonatal morbidity and mortality, caesarean section and vaginal instrumental delivery rates, maternal quality of life and costs. Analysis will be intention to treat. The power calculation is based on an expectant reduction of the maternal composite endpoint from 5% to 1% for an expected increase in neonatal RDS from 1% at 37 weeks to 10% at 34 weeks. This implies that 680 women have to be randomised.

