### Statistical issues

#### Data analysis

Data will be analysed on an intention-to-treat basis. Analysis of data includes comparison of maternal baseline characteristics at randomisation, maternal morbidity and mortality until hospital discharge and 6 weeks post-partum, neonatal morbidity and mortality until hospital discharge, method of delivery, type of hospital care and days of maternal and neonatal hospital stay. Differences between groups with normally distributed data will be tested using the Student's *t *test and for data with a skewed distribution, a non-parametric Mann-Whitney U test will be used. Categorical data will be analysed with χ2 statistics. Calculation of the percentages will be based on the number of valid observations. Treatment effect will be presented as relative risk (RR) with 95% CIs, and where appropriate as absolute risk reduction with 95% CIs and number needed to treat. A p-value of less than 0.05 indicates statistically significance. To asses treatment effects between different categories of patients in the trial we will perform subgroup analysis: per gestational age of the fetus per week (34^+0 ^- 34^+6^, 35^+0 ^- 35^+6 ^and 36^+0 ^- 37^+0^), parity (women with versus women without a previous vaginal delivery), hypertensive related disease (gestational hypertension versus pre-eclampsia), the use of corticosteroids (administered prior to delivery versus no use), mode of delivery (vaginal delivery versus caesarean section), caesarean delivery in history (history of a caesarean delivery versus no history of caesarean delivery) and the Bishop score (< 2, 2-6 and > 6).

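### The outcome list and the planned analysis name neonatal death only, so a fetal death after randomisation is not an event in the mortality or RDS comparison, although one arm has longer fetal time at risk

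*Protocol article*

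**What the plan says.** Four places in the protocol article speak of death of the child.

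- **Abstract, Methods/Design.** The child outcomes are given as "respiratory distress syndrome (RDS), neonatal morbidity and mortality".
- **Outcome measures, secondary outcomes.** The neonatal list closes with "admission to the neonatal intensive care unit (NICU) or neonatal death".
- **Data analysis.** For the child, the comparison covers "neonatal morbidity and mortality until hospital discharge".
- **Follow-up of women and infants.** The wording is wider: "Mortality and morbidity will be specified for the mother and the child until date of discharge from hospital and six weeks postpartum".

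No section names fetal death, stillbirth or perinatal death.

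Three other statements matter here. The neonatal primary outcome is RDS, and "Diagnosis of RDS requires signs of respiratory distress, consistent radiologic features" together with a period of oxygen therapy. The denominator rule reads "Calculation of the percentages will be based on the number of valid observations", in a section that also states intention to treat. In the intervention arm "labour will be induced within 24 hours after randomisation", while the expectant arm may continue to 37+0 weeks.

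**The concern.** Randomisation takes place with a living fetus, and the randomised contrast is how long the pregnancy continues. The fetus therefore stays at risk in the womb for longer in one arm than in the other. The article plans for fetal danger elsewhere. Signs of fetal compromise exclude a woman at entry, similar signs are grounds for ending expectant monitoring, and fetal heart rate is checked at least twice a week in that arm. The gravest event that this monitoring watches for is nevertheless absent from the named outcomes.

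The named child outcomes are mainly conditions of a live-born baby, where earlier birth is expected to do harm. If deaths before birth are not events, harms of early delivery are counted and the worst fetal harm of waiting is not. The trial's stated purpose is to weigh maternal benefit against harm to the child, so the side of the balance that favours waiting could look better than it is.

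**Working it through.** The article gives no figure for fetal death, so there is no stated figure to reproduce. The check has three parts.

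**1. Time at risk (Eligibility Criteria; Interventions).** Entry is from 34+0 to 36+6. The intervention arm is induced within 24 hours. The expectant arm may wait to 37+0:

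- entry at 34+0: 37+0 − 34+0 = 21 days
- entry at 36+6: 37+0 − 36+6 = 1 day

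The arms differ most for early entrants and hardly at all for the latest.

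**2. Expected number of fetal deaths.** 680 women randomised 1:1 (Sample size; Procedures) gives 680 / 2 = 340 per arm, treated here as singletons. The death rate r in the expectant arm is an assumption. Expected deaths = 340 × r, and P(at least one) = 1 − (1 − r)^340.

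| Assumed r | Expected deaths | P(at least one) |
|---|---|---|
| 0.1% | 0.34 | 29% |
| 0.2% | 0.68 | 49% |
| 0.5% | 1.7 | 82% |

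Multiple pregnancies are eligible, so the number of fetuses would be somewhat higher than 340.

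**3. Effect on the RDS comparison.** The Sample size section expects RDS of about 10% at 34 weeks and 1–3% at 37 weeks. As an illustration, take 34/340 RDS after induction and no fetal deaths there. In the expectant arm take 10 RDS events (340 × 0.03, rounded) or 3 (340 × 0.01, rounded), with k = 1 to 3 fetal deaths. The relative risk (RR) is induction over expectant.

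| Expectant RDS events | Handling of the k deaths | Expectant rate, k = 1 to 3 | RR, k = 1 to 3 |
|---|---|---|---|
| 10 | kept as non-events, 10/340 | 2.94% | 3.40 |
| 10 | left out, 10/(340 − k) | 2.95% to 2.97% | 3.39 to 3.37 |
| 10 | RDS or death, (10 + k)/340 | 3.24% to 3.82% | 3.09 to 2.62 |
| 3 | kept as non-events, 3/340 | 0.88% | 11.3 |
| 3 | left out, 3/(340 − k) | 0.88% to 0.89% | 11.3 to 11.2 |
| 3 | RDS or death, (3 + k)/340 | 1.18% to 1.76% | 8.5 to 5.7 |

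The choice between leaving the deaths out and keeping them as non-events scarcely matters. Under both, the deaths are not events. Counting them as events is what moves the result.

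**The case against.** The strongest reply has five parts.

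- **The event is not wholly lost.** A reader might infer that a fetal death counts in no outcome at all. The documents do not support that. The follow-up section covers mortality of the child without limiting it to live births, and a stillborn child might be scored under "a 5-minute Apgar score of 3 or below", though its handling is not stated. This stands. It does not put the death into the named death outcome, and it leaves the follow-up section wider than the outcome list and the analysis.
- **The RDS denominator is not fixed.** A reader might infer that stillborn children drop out of the RDS comparison. The text states both intention to treat and valid observations, and does not say which governs here. Such detail may properly sit in an analysis plan that is not shown. This stands too, but the death is a non-event under either reading.
- **The effect on RDS is negligible.** Correct for RDS itself. The RR changes materially only for RDS or death, which is a different endpoint. That is why RDS should remain the neonatal primary outcome.
- **The rate is assumed and the counts are tiny.** Also correct. One might argue that the counting rule could reverse the mortality comparison, for example 1 neonatal death after induction against 2 fetal deaths under monitoring being shown as 1 v 0. Two or more fetal deaths among 340 have a probability of only about 5%, 15% and 51% at 0.1%, 0.2% and 0.5%, and neither 1 v 0 nor 1 v 2 would be informative in a trial of this size.
- **The harm need not be nearly confined to waiting.** The article gives no rate by arm. High-risk fetuses are excluded, monitored women can be delivered on deterioration, and late entrants have almost equal time at risk. The supportable statement is longer fetal time at risk in the expectant arm.

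None of this supplies the missing outcome. The secondary list and the analysis section state the child-death outcome explicitly, and they state it as neonatal.

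**Conclusion.** The point holds in this form: the named death outcome and the planned mortality analysis for the child are neonatal only, fetal death after randomisation is not named, and the follow-up section is wider than both. Followed as written, such a death is an event in neither the mortality nor the RDS comparison, so the child-outcome comparison can flatter waiting.

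The expected number is small and rests on an assumed rate: 0.3 to 1.7 deaths in the expectant arm at 0.1% to 0.5%, with a 29% to 82% chance of at least one. The direction of the bias follows from the longer time at risk, which is up to 21 days for entry at 34+0 and about one day for entry at 36+6. The RDS percentage is practically unaffected. The maternal primary outcome, the sample size and the RDS definition are not touched by this point.

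**What to change.** In the secondary outcomes and in the Data analysis section, replace neonatal death or mortality with: perinatal death, defined as fetal death after randomisation or neonatal death, counted from randomisation among all fetuses alive at randomisation. Tabulate fetal and neonatal deaths separately by arm. This also brings both sections into line with the follow-up section.

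Keep RDS as the neonatal primary outcome and report RDS or perinatal death beside it as a supportive analysis, with the same denominator of fetuses alive at randomisation, so that a death is not read as freedom from RDS.

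The cost is wording only, since delivery details are already recorded in the CRF. The drawback is that the mortality outcome mixes fetal and neonatal deaths, which the separate tabulation handles. Because the trial is open label, the rule should be set before outcome data by arm are examined.
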